#### Randomization and blinding

Simple randomization will be applied using computer-generated random numbers [34], with a 1:1:1 allocation ratio. Simple randomization has proven to be reliable to large clinical research, generating similar numbers of subjects per group [34]. Participants will be randomly assigned to *en_línea* program, standard group therapy or control group. Randomization will be carried out by an independent researcher of the study. Therapists will not know the patient allocation until the coordinator inform them to begin the treatment. Thus, blinding will not be possible for the therapists during the intervention.

Currently, this study is in the recruitment phase. No statistical analysis have been performed at this time.

#### Assessment instruments

The questionnaires used in the assessment phase, apart from a sociodemographic questionnaire ad hoc*,* will be the following in its Spanish version:
E-TONA structured interview: a self-reported adaptation for adults will be used. This tool was designed to assess behavioral eating habits, physical activity, sedentary behaviors and health problems in fathers and children [35]. Only the behavioral eating habits data will be used in this study. The items of this descriptive and no diagnostic interview are multiple or dichotomous choice.The Temperament and Character Inventory Revised (TCI-R) [36, 37]. 240 items answered in a 5-Likert scale (1 = completely false; 5 = completely true). It includes seven main dimensions, 4 temperaments and 3 characters, with their corresponding specific features.Bulimic Investigatory Test Edinburgh (BITE) [38, 39]. Self-reported 33 item questionnaire, designed to identify bulimic symptoms: presence of binge eating and symptoms severity. Items are answered on different Likert scales or dichotomous choice.Stages of Change for Weight Management (S-Weight) [40]. Questionnaire of 5 excluding items to classify participants in one of the 5 stages of change for weight management.Process of Change for Weight Management (P-Weight) [40]. 33 items answered in a 5-point Likert scale to assess attitudes and behaviors to control weight.Night Eating Questionnaire (NEQ) [41, 42]. Self-reported 14 items scale to assess behavioral and psychological symptoms of Night Eating Disorder.SF-36 Health Survey (SF-36) [43, 44]. 36 items to assess functional health and wellbeing from the perspective of the respondent. It includes 8 scales related with the main aspects of heath, both physical and mental health.Coping Inventory Strategies (CSI) [45, 46]. 40 items tool answered on a 5-Likert scale (0 = not at all; 4 = totally), to assess 8 different coping strategies.Dutch Eating Behavior Questionnaire (DEBQ) [47, 48]. 33 item questionnaire answered in a 5-point Likert scale (1 = never; 5 = very often), to assess different types of intake.Depression Anxiety Stress Scale (DASS-21) [49, 50]. 21 item questionnaire answered in a 5-point Likert scale (0 = nothing applicable to me; 5 = applicable to me most of the time), to evaluate the severity of depression, anxiety and stress experimented during the last week.

### Statistical analysis

To estimate the sample size has been used the primary outcome, weight loss differences between baseline and post-treatment measures. The range of the effect size of the intervention will be 0.5 SD in group comparisons, alpha 5% and two-tail tests [51]. These data determine that we need at least 88 patients per group, considering an expected 31% dropout rate [52], our final choice will be *N* = 305 [53].

Analysis will be performed using STATA/IC 14.2. All data will be checked for missing values, accuracy and normality criteria. Intention to treat analysis (ITT) will be used to analyze the data, including all randomized participants. After that, per protocol analysis will be performed for participants who have completed 17 weeks follow-up. ANOVA for repeated measures, with type of intervention as independent variable and time (baseline and follow-up visits) as dependent variable, will be conducted to analyze primary and secondary outcomes.

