**Methods:**

This is a randomized controlled trial with three intervention arms: *en_línea,* standard group therapy and control group. To perform this study, 305 adults (18–65 years) with overweight type II (27–29.9 kg/m^2^) or obesity type I (30–34.9 kg/m^2^) will be invited to participate. Interventions will last 17 weeks with follow-ups 1, 3, 6 and 12 months after the post-treatment appointment. The primary outcome will be post-treatment weight loss and the maintenance during the follow-ups. Secondary outcomes will be adherence rates, drop outs and quality of life. Participants will be assessed before randomization and they will be sign an inform consent.

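### N = 305 does not follow from 88 per group and 31% dropout: it leaves about 70 per group, not 88

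*Protocol article*

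**What the plan says.** The Statistical analysis section of the protocol article sizes the trial on the primary outcome, described as "weight loss differences between baseline and post-treatment measures". The design inputs are given in one sentence: "The range of the effect size of the intervention will be 0.5 SD in group comparisons, alpha 5% and two-tail tests". The result follows: "we need at least 88 patients per group, considering an expected 31% dropout rate [52], our final choice will be" 305.

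The Abstract (Methods) repeats the total: "To perform this study, 305 adults". The Background and the section on randomization and blinding both give three arms with 1:1:1 allocation. The analysis is intention to treat on everyone randomised, followed by a per-protocol analysis of those who completed 17 weeks. No power is stated anywhere.

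**The concern.** The paragraph gives a per-group minimum, a dropout rate and a total, and presents the total as the consequence of the other two. Going from 264 to 305 is far too small a step for a 31% loss. A reader would take 88 per group with a post-treatment weight as the trial's size, when the plan's own dropout assumption leaves about 70.

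This bears on the primary outcome, which includes differences in weight loss between the three arms. The article also says that recruitment is under way and that nothing has been analysed, so the target can still be corrected without knowledge of results.

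**Working it through.** **Inputs, all from the Statistical analysis section unless noted**

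- Minimum per group: 88 ("we need at least 88 patients per group")
- Dropout: 31% ("considering an expected 31% dropout rate")
- Total: 305 (also in the Abstract)
- Arms: 3, allocated 1:1:1 (Randomization and blinding)
- Effect: 0.5 SD between groups; "alpha 5% and two-tail tests"
- Power: not stated

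**Step 1. Try to reproduce 305**

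Required total before dropout: 3 × 88 = 264.

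| Route | Calculation | Total |
|---|---|---|
| Standard inflation, N/(1 − d) | 264/0.69 = 382.6 | 383 |
| Same, rounded up by arm | 88/0.69 = 127.5, so 3 × 128 | 384 |
| Common mistake, N × (1 + d) | 264 × 1.31 = 345.8 | 346 |
| 88 taken as already inflated | 3 × 88 | 264 |

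None gives 305.

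**Step 2. Work forward from 305**

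- Randomised per arm, on average: 305/3 = 101.7
- Remaining after 31% loss: 305 × 0.69 = 210.45, and 210.45/3 = 70.15 per group
- Shortfall against the stated minimum: 88 − 70 = 18 per group
- Shortfall in randomised participants: 383 − 305 = 78, or 384 − 305 = 79
- Dropout at which 305 would keep 88 per group: 1 − 264/305 = 13.4%

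**Step 3. What could lie behind 305**

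Two back-calculations land on it: 3 × 70/0.69 = 304.3, and 264 × 1.155 = 304.9 (an add-on of half of 31%). The article states neither, so these are only guesses at where the slip occurred.

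**Step 4. What the difference is worth**

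The article names neither the power nor the test behind the 88. We assume a pairwise two-sample t-test with a standardised difference of 0.5. The last column also assumes a Bonferroni correction for three comparisons, which the article does not state.

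| Per group | Power, two-sided 5% | Difference detectable with 90% power, two-sided 5% | Power at alpha 0.05/3 |
|---|---|---|---|
| 88 | 91.0% | 0.49 SD | 81.5% |
| 70 | 83.6% | 0.55 SD | 70.3% |

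For reference, the same unadjusted test needs 64 per group for 80% power and 86 for 90%, so 88 is not exactly the answer to either usual target.

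As a check on the choice of test, take a one-way three-group ANOVA with means spanning 0.5 SD and the middle arm halfway. Then f = 0.5/√6 = 0.204, and power is about 85% with 88 per group and 75% with 70.

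**The case against.** Nobody can get from 88, three arms and 31% to 305 by a standard route, so the other side can only contest the consequences.

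- **The power figures are ours.** The article states no power and plans a repeated-measures ANOVA, so 91% and 84% describe an assumed pairwise t-test. This stands. The only shortfall the document itself fixes is the one against its minimum of 88.
- **It is not known which figure is wrong.** Since 70 per group with 31% dropout leads to about 305, the 88 may be the slip and the trial may be the size that was intended. This also stands, and it favours restating the paragraph over enrolling more.
- **Intention to treat keeps all randomised participants, about 102 per arm.** This stands in part. Depending on how missing weights are handled, the loss of information could be smaller than a pure completer count suggests. It does not remove the contradiction, because the plan itself adds participants to cover dropout, and an analysis set does not supply a week-17 weight that was never measured.
- **Arm sizes are random under simple randomization.** True, so 102 and 70 per arm are expected values. The mismatch in the totals is unaffected.
- **Unadjusted pairwise power stays above 80%.** True on our assumptions. The case therefore rests on the paragraph contradicting itself, not on the trial being too small to run.

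That an article condenses a fuller protocol is no answer here. The inputs and the result are all printed, and they disagree.

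**Conclusion.** The concern holds. Under the plan's own 31% dropout, 305 randomised leaves about 210 participants, or 70 per group, not the 88 given as the minimum. Keeping 88 would need 383 or 384 randomised. This part rests only on figures in the article and on three equal arms.

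The cost in power is about 7 percentage points for an unadjusted pairwise comparison (91.0% to 83.6%) and about 11 if three comparisons are Bonferroni-adjusted (81.5% to 70.3%). Those figures depend on the assumed test and on treating dropouts as contributing no post-treatment weight. The paragraph must be corrected because the stated size is one the design does not deliver.

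**What to change.** Restate the sample-size paragraph so that its figures agree, keeping the enrolment target. For example: *305 participants will be randomised (about 102 per arm). With 31% dropout, about 210 (70 per arm) are expected to have a week-17 weight, which gives about 84% power for a pairwise difference of 0.5 SD at two-sided 5%, without adjustment for multiple comparisons.* Remove 88 as the evaluable number per group. The sponsor should confirm the test and power used in the calculation. If another test or a multiplicity adjustment was intended, the power in that sentence should be replaced to match.

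If the sponsor does want 88 evaluable per group, the total should instead become 384 (128 per arm), here and in the Abstract.

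The restatement costs only wording and a less favourable evaluable number; no one extra is enrolled. The alternative costs 79 more participants.

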Previous reviews have reported effectiveness results of web-based computer-tailored interventions [7–9, 18–20]. These investigations concluded that web-based weight control programs are more effective than control or minimal contact interventions [18, 19]. However, effectiveness results are short-term and adherence is too low comparing with traditional interventions or web-based programs with an extra component, like group reinforcement sessions [7–9, 20]. Web-based interventions with personalized feedback, delivered by a health professional, have reached better results than those without feedback or automatized feedback [9–11]. Therefore, internet could be an innovative and promising way to deliver weight control interventions, but further investigation is need [21].

We have developed a web-based computer-tailored intervention aimed to acquire healthy long-term habits. The body mass index (BMI) of the target population must be between 27 and 34.9 kg/m^2^, namely overweight type II or obesity type I [22]. To design a potentially successful program, basic behavior change aspects have been included: nutrition, physical activity, self-recording and goal setting [7, 23]. Perceived family and friends support were shown particularly helpful during the process of health behavior change [10, 11, 24], and it should be considered during treatment design. Finally, psychological aspects like dealing with negative self-talk must be driven by a healthcare professional, providing personalized feedback and a non-judgmental attitude [9–12]. One of the most tested lifestyle change intervention for weight management is the LEARN program [25]. The word LEARN is an acronym of the five main treatment areas: Lifestyle, Exercise, Attitudes, Relationships and Nutrition [25]. This program is a self-help book which includes basic treatment areas [7, 23], and also includes social support as a relevant aspect to achieve long-term lifestyle changes [10, 11, 24].

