### Outcomes

#### Primary outcomes measures

The primary outcome is the weight loss. First, differences between the pre and post measures for each treatment arm. Treatment success is defined as 5–10% of weight loss respect the initial weight. Then, significant differences in weight loss and other anthropometric measures, specified later, between the three treatment arms. Finally, the maintenance of weight loss during the follow-ups, significant differences between the three treatment arms.

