### Study design and randomization

#### Procedure

Participants will be recruited through advertising (flyers, posters, University website, workplace-based emails and social networks). Obese and overweight people interested in participating in the study must send an email to the coordinator of the project. Participants will receive an email to attend an appointment with a psychologist. In this first appointment, patients will be informed about the aims and characteristics of the study, they must sign the written informed consent and, after that, a brief interview and baseline anthropometric measures will be taken. Anthropometric measures will be weight, height; and, neck, chest, waist, hips, leg and arm circumferences. All measures will be taken with the participant wearing light clothing and without shoes. Height will be taken with 1 cm using a stadiometer. Weight will be measured on a digital scale. Circumferences measurements will be measure following the indications provided by WHO [33].

To ensure the accomplishment of inclusion and exclusion criteria participants must answer a large battery of questionnaires specified later. These questionnaires are divided in two batches. After the first in-person appointment, participants will receive an email with the instructions to complete the first batch of questionnaires, they will be provided with an identity number for data protection and with the direct link to the available questionnaires in the platform SurveyMonkey. After the completion of the first part, a second email with the link to the second batch of questionnaires will be sent.

Assessment phase will last 2 weeks, selected participants will be randomized to one of the three study arms. Patients will receive an email with information about their belonging group. Obese and overweight people randomized to *“en_línea”* program, must assist to a 1 h training session to get familiar with the website and the mobile application. When participants are included in the study, both *en_línea* and group intervention, they will be given timings for follow-up meetings during the treatment at week 8 and week 17. After interventions finish, follow-up meetings will be happened at 1, 3, 6 and 12 months. In the follow-up visits a brief interview and anthropometric measures will be taken again, the duration of these meeting will be between 15 and 30 min (Fig. 3).

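### The one repeated-measures ANOVA named for all outcomes cannot show whether arms differ in maintenance of weight loss, because its group-by-time term can reject on the week-17 difference alone

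*Protocol article*

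**What the plan says.** The section on primary outcome measures lists three questions in turn: the pre-to-post change within each arm, the difference between arms in that loss, and then "Finally, the maintenance of weight loss during the follow-ups, significant differences between the three treatment arms". It gives no metric, reference visit or contrast for the third.

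The Statistical analysis section names one method, "ANOVA for repeated measures, with type of intervention as independent variable and time (baseline and follow-up visits) as dependent variable", and says that it "will be conducted to analyze primary and secondary outcomes". It does not say whether the group, time or group-by-time term answers each question. The sample size rests on "weight loss differences between baseline and post-treatment measures", with "The range of the effect size of the intervention will be 0.5 SD in group comparisons", so maintenance played no part in it.

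The Procedure section uses the word follow-up for two sets of visits. One is "follow-up meetings during the treatment at week 8 and week 17", stated for the en_línea and group-therapy arms. The other is described thus: "After interventions finish, follow-up meetings will be happened at 1, 3, 6 and 12 months".

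**The concern.** The null hypothesis of the group-by-time term is that the arm profiles are parallel from baseline through every visit in the model. Week 17 has to be one of those visits, or the pre-to-post outcome would have no test. A difference at week 17 therefore makes the null false, even if the arms are identical at 1, 3, 6 and 12 months. A significant term says that the arms differed in change at some time. It does not say that they differed in maintenance.

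This distinction is central to the trial. The Background criticises earlier web programmes on exactly this ground: "However, effectiveness results are short-term and adherence is too low comparing with traditional interventions". The Discussion expects better long-term results from en_línea. If an all-visit test is read as the maintenance result, a benefit that is gone by the first follow-up could pass for a lasting one.

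**Working it through.** **Inputs from the protocol.** Effect 0.5 SD, two-sided 5%, at least 88 per group, 31% dropout, N = 305, allocation 1:1:1.

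**The plan's own figure.** For 0.5 SD at two-sided 5%, a t-test needs 64 per group at 80% power and 86 at 90%. The stated 88 is thus close to 90% power, which the protocol does not state. The total does not follow: 3 × 88 = 264, and 264/0.69 = 383, not 305. That is a separate matter. Here it only sets the arm sizes: 305 × 0.69 / 3 ≈ 70 completers per arm, or 305 / 3 ≈ 101 if all are kept.

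**Assumptions not in the protocol.** Both active arms are better than control by 0.25 SD of weight change at week 8 and 0.5 SD at week 17. After that the difference is either zero at all four follow-ups (lost) or 0.5 SD at all four (kept). Data are complete.

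**Closed form under compound symmetry.** Let d_t be the active-minus-control difference at visit t, in units of the SD of change. The error variance per visit is then 0.5 in those units. With two equal active arms, the squared arm deviations sum to (2/3)² + (1/3)² + (1/3)² = 2/3 per unit d². The noncentrality of the group-by-time test is

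λ = n × (2/3) × Σ(d_t − mean d)² / 0.5.

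- Lost: d = (0, 0.25, 0.5, 0, 0, 0, 0). Σd² = 0.3125, and 0.75²/7 = 0.0804. The difference is 0.2321.
- Kept: d = (0, 0.25, 0.5, 0.5, 0.5, 0.5, 0.5). Σd² = 1.3125, and 2.75²/7 = 1.0804. The difference is 0.2321.

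The two are equal, because one profile is the mirror image of the other. With n = 70, λ = 70 × 0.6667 × 0.2321 / 0.5 = 21.67 on 12 and 1242 degrees of freedom, and the rejection rate is 0.89 in both cases. Leaving out week 8, the sums are 0.25 − 0.5²/6 = 0.2083 (lost) and 1.25 − 2.5²/6 = 0.2083 (kept). Then λ = 19.44 on 10 and 1035 degrees of freedom, and the rate is 0.88 in both. Under this error structure the test cannot tell a lost effect from a kept one.

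**Other correlation structures, by simulation** (Greenhouse-Geisser correction for group-by-time, 70 per arm, nominal 5%). The structures run from weights that drift like a random walk to changes correlated 0.9 between adjacent visits.

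| Test | Effect lost after week 17 | Effect fully kept |
|---|---|---|
| Group-by-time, baseline and all visits | 33–97% | 38–92% |
| Group main effect, same model | 5–7% | 14–21% |
| Between-arm test of change from baseline to 12 months | 4–6% | 34–88% |

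The last row covers compound symmetry and random-walk errors only. At 101 per arm, under the same two structures, group-by-time rejects in 70–98% of trials when the effect is lost. Only the 12-month test stays at its nominal level when the effect is lost and gains power when it is kept. The main effect averages over baseline and every visit and carries all the between-person variation in weight, so it has little power and does not isolate the follow-up period.

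**The case against.** The strongest reply is that the protocol is a condensed article. It never mentions a group-by-time term and never says that one p-value settles maintenance. Visit-specific contrasts after a repeated-measures ANOVA are ordinary content of an analysis plan. Part of this stands: it is not known that the overall test would be used this way. But the article does more than stay silent, since it assigns this one method to a named part of the primary outcome, and no single overall term of that method answers the question.

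The visit set is also open. The abstract uses follow-ups for months 1 to 12 only. With baseline and those four visits alone, the interaction rejects in about 4% of trials when the effect is lost. That reading, however, leaves the pre-to-post outcome without a test. The week-8 visit is not stated for the control arm, but dropping it hardly changes the result.

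A reader might go further in three ways that the documents do not support:

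- That the ANOVA rejects whenever arms differ at week 17. It does not: the rate depends on sample size and correlation, and the main effect rejects in only about 5–7%.
- That a short-term benefit would be reported as maintenance. The protocol states no such decision rule.
- That rejecting when all arms regain equally from unequal week-17 losses is an error. If maintenance means a difference still present at follow-up, that is correct detection.

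**Conclusion.** The point holds in limited form. As written, a significant repeated-measures ANOVA does not show a between-arm difference in maintenance. The group-by-time term can be driven by the week-17 difference alone, and it rejects about as often for a lost effect as for a kept one (33–97% against 38–92% at 70 per arm). The main effect is not a substitute.

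The rates rest on an assumed 0.5 SD at week 17, complete data and assumed correlations. The logic does not depend on them: a null hypothesis that includes week 17 is false once arms differ there. This is a weakness in how a primary question is tied to its test, and it should be corrected. It is not evidence that a wrong conclusion will be drawn.

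**What to change.** In the sections on primary outcome measures and statistical analysis, state that maintenance is not judged by the overall ANOVA. Prespecify between-arm contrasts of weight change from baseline at the post-treatment follow-ups (en_línea against control, and en_línea against group therapy), taken from the same longitudinal model, each with a 95% confidence interval. Name one as key. Twelve months is a natural example because it is the last visit, but the outcome refers to the follow-ups in general, so the choice is the sponsor's. Report the other follow-ups and the change from week 17 to 12 months as supportive.

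This changes wording only. No new data are needed, and the article says that recruitment is under way and no analysis has been done. The small downside is that a visit-specific contrast may make a maintenance claim harder to reach. With random-walk errors at 70 per arm and the effect kept, the 12-month test rejects in about 34–35% of trials, against 43–46% for group-by-time. The latter figure is not power for maintenance, since that test rejects about as often when the effect is lost.

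### The plan promises intention-to-treat on all randomised participants, but the only model it names, a repeated-measures ANOVA, falls back largely to completers at 31% dropout, and time is wrongly called the dependent variable

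*Protocol article*

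**What the plan says.** All of this stands in the Statistical analysis section of the protocol article.

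- Population: "Intention to treat analysis (ITT) will be used to analyze the data, including all randomized participants". Afterwards a "per protocol analysis will be performed for participants who have completed 17 weeks follow-up", so the two sets are meant to differ.
- Model: "ANOVA for repeated measures, with type of intervention as independent variable and time (baseline and follow-up visits) as dependent variable, will be conducted". It is the only model named, and it serves both the primary and the secondary outcomes.
- Missing data: "All data will be checked for missing values, accuracy and normality criteria". No imputation or likelihood-based method is named.
- Size: "we need at least 88 patients per group", "considering an expected 31% dropout rate", and "our final choice will be *N* = 305". The calculation is based on the weight difference between baseline and post-treatment, with an effect of 0.5 SD.

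Elsewhere, Procedure schedules meetings at weeks 8 and 17, naming the en_línea and group arms, and then follow-ups at 1, 3, 6 and 12 months. Primary outcomes measures covers both the pre-post weight loss and its maintenance over follow-up, compared between the three arms.

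**The concern.** The promised population and the named model pull in different directions. A classical repeated-measures ANOVA needs a value at every occasion, so with substantial dropout it analyses completers, whatever the population is called. The ITT result would then add little to the per-protocol result, and the protection expected from ITT would be lost.

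This matters because the arms differ sharply in contact: weekly personal feedback in en_línea, ten 90-minute sessions in the group arm, and a newsletter without feedback in the control arm. It is plausible, though not shown in the document, that people who lose little weight leave one arm more readily than another. A comparison of completers would then flatter the arm from which they leave.

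The model sentence is also wrong as written. Weight (or another outcome) is the dependent variable, and time is a within-subject factor. Finally, no contrast is singled out. With three arms and up to seven occasions (baseline, weeks 8 and 17, four follow-ups) the arm-by-time test has up to (3 − 1) × (7 − 1) = 12 numerator degrees of freedom, whereas the sample size rests on one change, baseline to post-treatment.

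**Working it through.** **1. How many participants a complete-visit ANOVA keeps.** Inputs from the plan: N = 305, dropout 31%.

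305 × (1 − 0.31) = 305 × 0.69 = 210.45, so about 210 in total, about 70 per arm. About 95 randomised participants are left out.

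This is an upper limit. The plan does not say at which visit the 31% applies, and anyone who misses a later visit is lost as well. If, as an assumption, 40% miss at least one visit up to 12 months, 305 × 0.60 = 183 remain. Where week 17 is one of the occasions, the complete-visit set cannot be larger than the set of 17-week completers.

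The plan's own sample-size figures do not agree with each other: 3 × 88 = 264, and 264 / 0.69 = 383, not 305. That is a separate matter and nothing here depends on it.

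**2. Does long format rescue the promise?** In one simulated data set of 305 participants, those who dropped out had a baseline weight only. A least-squares model with subject, time and arm-by-time terms was fitted twice.

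| Participants in the fit | Residual df | Residual mean square | Arm-by-time estimates |
|---|---|---|---|
| all 305 | 416 | 6.062689 | −2.700797, −1.300356, −1.601487, −1.754194 |
| 211 with follow-up | 416 | 6.062689 | identical |

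So participants with only a baseline weight add nothing to the treatment effect. Participants who also have a week-8 weight do contribute; step 3 covers them.

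**3. How large a bias could be.** None of the following settings comes from the document. Two arms of 102, no true difference, SD of weight change 3 kg at week 8 and 5 kg at week 17, correlation 0.75, 31% dropout in each arm. The log-odds of dropout rise, per SD, as week-8 weight loss gets smaller, with the slopes shown. Completers are compared at week 17.

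| Slope, arm A / arm B | Completer bias (kg) | In SD (bias / 5) | Type I error |
|---|---|---|---|
| equal in both | 0 | 0 | about 5% |
| 1.0 / 0.7 | about 0.24 | about 0.05 | about 6% |
| 1.0 / 0.5 | about 0.4 | about 0.08 | about 8% |
| 0.7 / 0 | about 0.75 | about 0.15 | about 12 to 15% |
| 1.2 / 0 | about 1.1 | about 0.22 | about 27 to 28% |

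With dependence in one arm only, the long-form ANOVA with subject terms (baseline, weeks 8 and 17) has a bias of about 0.47 to 0.68 kg. That is roughly 40% less than for completers, but not zero. A likelihood analysis that uses the week-8 weight is unbiased in every row. This is expected, because dropout was generated as missing at random given that weight.

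**The case against.** **ITT and this ANOVA are compatible if missing weights are imputed first.** The article does not prescribe a complete-case analysis, and missing-data handling is often left to an SAP. A reader might infer that the ANOVA cannot deliver ITT at all. The document does not support that: imputation in an unseen SAP, or a long-form fit, would keep more participants in. What stands is that the article fixes both the population and the model, and that the pair as published does not fit together at the dropout it expects.

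**The bias is conditional.** A reader might infer that a completer analysis is biased here in any case and inflates the false-positive rate. It is not if dropout works alike in each arm, and it is small if the mechanisms differ only moderately. The largest figures need dropout to depend on weight loss in one arm and not at all in the other. This objection stands in full, so the size must be given as a range.

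**The omnibus test is not beside the point.** A reader might infer that it fails to answer the primary question. Maintenance over follow-up, compared between arms, is part of the primary outcome, and an arm-by-time test bears on it. What remains is that it does not isolate the baseline to week-17 contrast on which the trial is sized.

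**Calling time the dependent variable looks like a drafting slip.** The bracketed list of visits suggests that an arm-by-time design was meant. That is likely, but the sentence defines the primary analysis and has to be corrected.

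**A mixed model has limits too.** With baseline weight as a covariate it drops everyone without a post-baseline weight, which repeats the fault. Its advantage in the simulation also relies on a week-8 weight, and Procedure does not establish that visit for the control arm. Both points stand and shape the fix.

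**Conclusion.** The point holds in limited form. As published, the ITT promise and the named model do not match. At the plan's own dropout a classical repeated-measures ANOVA keeps at most about 210 of 305 and largely coincides with the per-protocol analysis. The long form softens this without curing it. The naming of time as dependent variable is a plain error.

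The mismatch rests on the document's own statements, read without any imputation step. The consequence for the treatment comparison rests on assumptions: from no bias, through about 0.05 to 0.1 SD, to about 0.15 to 0.22 SD with type I error of about 12 to 28% in the one-sided-mechanism case. The upper end is more than a third of the planned effect (0.19 / 0.5 = 0.38 at a mid-range bias of 0.19 SD). The document offers no evidence on which of these cases will apply, which is the reason to choose an analysis that depends on it less.

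**What to change.** 1. Correct the sentence: weight is the dependent variable; arm and time are factors.
2. Replace the ANOVA for weight by a linear mixed model for repeated measures with visit (categorical) and arm-by-visit effects. Include baseline weight as an outcome, with its mean constrained equal across arms, so that every randomised participant contributes. The choice of covariance structure can be left to the SAP.
3. Name the arm difference in change from baseline to week 17 as the primary contrast, which matches the sample-size basis, and read the maintenance contrasts from the same model.
4. State the missing-at-random assumption and add one sensitivity analysis for dropouts, for example baseline carried forward or reference-based imputation.
5. Confirm whether the control arm has weights at weeks 8 and 17, since Procedure names only the two active arms for those meetings. If it has no week-8 weight, the model has less to work with in that arm, and the sensitivity analysis carries more weight.

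The cost is rewording of the statistical section and a little more analysis work; the model is available in the Stata 14.2 already named. The Randomization and blinding section says that recruitment is under way and no analysis has been done, so the change can still be prespecified.
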